#### Intervention components

mNavigator comprises four key modules:
Pre-diagnosis module: This includes data entry forms that enable registration of new patients, collection of socio-demographic data and clinical history, entry of laboratory and imaging results at presentation, and assignment of a working diagnosis.Burkitt lymphoma (BL) module: This includes data entry forms specific to patients diagnosed with Burkitt lymphoma to document cancer staging, planned treatment (including details of the dose and timing of for each chemotherapy cycle), end of therapy evaluation, and follow up visit planning. Throughout the forms in this module, Burkitt lymphoma treatment guidelines are incorporated as prompts for data entry, computation of relevant lab values, adjustment of chemotherapy regimen, scheduling of chemotherapy cycles, and post-treatment follow up.Retinoblastoma (Rb) module: This module is similar to the Burkitt module, except that it is specific to patients diagnosed with retinoblastoma and incorporates the specific treatment guidelines for retinoblastoma.Non-BL/Rb module: This module includes data entry forms for patients who are not diagnosed with Burkitt lymphoma or retinoblastoma. The forms do not track the treatment of the patients or incorporate treatment guidelines. Rather, they enable tracking of patient demographics and outcomes.

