#### Informed consent

mNavigator will be used as the standard of care for patient intake and outcome tracking of pediatric cancer patients at BMC. All pediatric cancer patients at BMC will be registered and tracked in mNavigator. For research purposes, research staff (e.g., research coordinator, mNavigator users, etc.) will consent caregivers of any patients who receive a clinical diagnosis of Rb or BL for tracking their treatment information. Data for only those providing informed consent will be used in the research study (with the exception of historical data). For consenting patients, mNavigator will be used for treatment management with a typical treatment duration of 3 months for patient with BL and 4 months for patient with Rb.

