### Sample size and recruitment

Sample size estimates are based on the patient volume at BMC. Based on prior experience, approximately 150 new pediatric patients present each year for cancer management at BMC. Of these, approximately 50 patients are anticipated to have a diagnosis of BL or Rb. All new patients will be registered in mNavigator, and all patients with BL and Rb who provide informed consent will be tracked in the system for treatment management. Historical data is anticipated to be available for approximately 200 BL and Rb patients from 2015 to 2019 (i.e., 50 records/year). All available historical data will be used in the comparator arm. Similarly, approximately 15 health professionals at BMC are identified as individuals directly or indirectly impacted by mNavigator, all of whom will be approached for study participation. All prospective participants will be approached in person to provide study information and invite participation.

To ensure thematic saturation of qualitative data and that diverse perspectives are heard, we will complete an interview with parents of at least 12 BL and 12 Rb patients. Interviews may be recorded using an encrypted digital device.

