### Outcome measures

Study outcomes are summarized in Tables 3 and 4. Measurement of study outcomes is guided by the RE-AIM framework. In mNavigator, we will collect data points that will allow us to measure outcomes in the following domains:
Reach – e.g., proportion of eligible patients for whom protocol was used.Effectiveness – e.g., proportion of cases that abandoned care, with treatment completion and time from hospital presentation to confirmed diagnosisAdoption – e.g., proportion of providers who use the protocol, provider acceptability and satisfaction with mNavigator content, ease of delivery and credibilityImplementation/Compliance – e.g., proportion of protocol steps completed per patientMaintenance (measured in future studies)

**Table 3 Tab3:** Summary of outcomes related to intervention effectiveness and their measurement

Outcome	Measure	Data source
Change in protocol compliance (primary outcome)	Percent difference in protocol compliance with mNavigator and historical compliance. Protocol compliance is calculated as proportion of protocol steps completed, based on a compliance checklist.	mNavigator data from prospectively registered pediatric cancer patients from July 2019 – July 2020 and data extracted from paper charts for patients registered at BMC from 2015 – June 2019 entered into mNavigator
Change in treatment abandonment (secondary outcome)	Calculated as the difference in proportion of patients registered in mNavigator who abandoned treatment compared to historical controls who abandoned treatment. Treatment abandonment is defined as missing four or more consecutive weeks of treatment or follow-up while still on therapy.	Data from mNavigator (outcome form)
Change in treatment completion rate	Calculated as the proportion of patients registered in mNavigator who completed treatment compared to historical controls	Data from mNavigator (outcome form)
Change in time to diagnosis	Change in the number of days to diagnosis using mNavigator compared to historical controls. Time to diagnosis is computed as the duration from registration to diagnosis	Data from mNavigator (registration form; diagnosis form)

**Table 4 Tab4:** System-level outcomes related to the mNavigator application

Outcome	Measure	Data source
Usability^a^	System usability scale score ranging from 0 to 100. A SUS score above a 68 is considered above average and anything below 68 is below average.	10-point validated system usability scale

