Acceptability	Proportion of providers who would continue to use the app. Proportion of providers who would recommend the app to others.	Semi-structured interviews
Utilization	Number of forms submitted, stratified, by users, per month of implementation	Data from mNavigator (Mobile users statistics)
Reach	Number of patients registered in mNavigator during study period	Data from mNavigator (Mobile users statistics)
Stability	• Number of instances of mNavigator failure per month (all-causes) • Number of instances of CommCare failure per month (all-causes) • Number of instances of device • failure per month (all-causes)	Data from CommCare (Worker Activity and Daily Activity reports) cross checked with manual reports from Mobile users
Training	Number of hours of initial training as well as hours of ongoing support provided during the first month of Implementation	Manually recorded from Duke team members that are performing initial training
User-proficiency	Number of users who are proficient in use of mNavigator within first month of implementation	Data from CommCare (Worker Activity reports)
Time per form	Average time in minutes spent completing each form, stratified by form	Data from mNavigator (Mobile users statistics)
Time per patient	Total time in minutes spent entering patient data in mNavigator, from time of registration until an outcome is recorded. Calculated by summing time for completing each form by patient.	Data from mNavigator (Mobile users statistics)

^a^System Usability Scale developed by John Brooke is available from www.usability.gov

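### Table 4 measures Reach as a count of registrations, which has no eligible-patient denominator and does not respond to use of the BL/Rb protocol modules

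*Protocol article*

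**What the plan says.** Outcome measures says that measurement follows RE-AIM and that Tables 3 and 4 summarise the outcomes. Its list of domains has this entry: "Reach – e.g., proportion of eligible patients for whom protocol was used". Table 3 has no Reach row. Table 4, which covers system-level outcomes of the application, has one, and its measure is "Number of patients registered in mNavigator during study period", taken from the mobile user statistics.

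Three other sections determine what that count contains:

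- Informed consent (Phase 2): "All pediatric cancer patients at BMC will be registered and tracked in mNavigator". The same section limits research data to consenting patients, apart from historical data.
- Sample size and recruitment: "All new patients will be registered in mNavigator, and all patients with BL and Rb who provide informed consent will be tracked in the system". It expects that "approximately 150 new pediatric patients present each year for cancer management at BMC" and that "approximately 50 patients are anticipated to have a diagnosis of BL or Rb".
- Intervention components, on the module for children with other cancers: "The forms do not track the treatment of the patients or incorporate treatment guidelines". That module records demographics and outcomes only.

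**The concern.** The illustrated quantity and the tabulated one differ in three ways: a proportion against a count, eligible patients against everyone registered, and use of the protocol against entry in the system. Nothing in the article connects them.

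The study is meant to inform implementation at other tertiary centres. For that, a reader wants to know what share of the eligible children had their care run through the protocol module. If Table 4 is followed as written, the line labelled Reach will not say so. Caregiver refusal or a BL/Rb module that was never opened would lower the share of eligible children reached and leave the reported number where it was.

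**Working it through.** The article states no numerical Reach figure or target, so there is none to reproduce. The check compares the two quantities on the article's own volumes.

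**Inputs from the article**
- New pediatric cancer patients per year: about 150 (Sample size and recruitment).
- Of these, BL or Rb: about 50 (same section). Study setting gives a 35% share, and 150 × 0.35 = 52.5, which agrees with about 50 given the rounding.
- Registration: all patients, by plan.
- Historical BL/Rb records to be abstracted into mNavigator: about 200 (Sample size and recruitment; Quantitative data collection).

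**Step 1. Who is in the count.** 150 − 50 = about 100 registrants a year have another cancer. They receive the registration, pre-diagnosis and outcome-tracking parts of mNavigator, but no treatment protocol exists in their module. About two thirds of the count (100/150) therefore cannot contribute to protocol use.

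**Step 2. Response to protocol use.** Proportion = eligible patients managed by protocol / eligible patients, with a denominator of 50. The numerators below are assumptions, chosen to show the range.

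| Protocol module used for | Proportion of eligible | Table 4 count |
|---|---|---|
| 10 of 50 | 20% | about 150 |
| 20 of 50 | 40% | about 150 |
| 25 of 50 | 50% | about 150 |
| 40 of 50 | 80% | about 150 |
| 50 of 50 | 100% | about 150 |

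**Step 3. Response to registration.** Count = children presenting × share registered. With complete registration the count equals clinic volume: 100, 150 or 200 presenting give 100, 150 or 200. With incomplete registration it mixes the two: 150 × 1.00 = 150 and 200 × 0.75 = 150. The count alone cannot tell these apart.

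**Step 4. Abstracted records.** Historical charts are entered into the same system. The Table 4 row refers to the study period but does not say that these entries are left out. If a system total included them, it could reach about 150 + 200 = 350.

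**Step 5. Whether another measure supplies the proportion.** Utilization counts forms by user and month. Time per form is broken down by form, so a form that was never used would show. The planned fidelity data describe how the system was used in practice. The primary outcome scores protocol steps completed. All of these bear on module use, but none has eligible patients as its denominator.

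**The case against.** The strongest reply is that there is no contradiction. The text offers the proportion as an example of what the Reach domain covers and does not define Reach by it. Table 4 concerns the application as a system, and an application-level count can stand beside a domain-level proportion. The qualitative analysis plan also mentions observation data as helping to assess reach. This stands in part: a reader might infer two rival fixed definitions, and the article does not support that. What remains is that the only row with a measure and a data source uses the count, and nothing commits the authors to reporting the proportion.

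Four stronger readings are tempting and go too far:

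- *The count includes children who cannot receive the intervention.* Children with other cancers do use parts of mNavigator, and those parts are listed among its components. They lack only the treatment-guideline part, so counting them is coherent for the application's own footprint.
- *The count measures clinic volume and nothing else.* That holds only if registration is complete. Complete registration is planned, not yet observed, and the count can be read roughly against the expected 150.
- *Reach would be reported as high even if it failed.* The article sets no target, so high has no meaning here.
- *Unused modules would go unseen.* Utilization, Time per form and the fidelity data would partly expose them. Refusals and never-registered children are what they would not clearly show.

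It is also fair to say that nothing in the article suggests low module use. The figures in Step 2 show how insensitive the count is and predict nothing.

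**Conclusion.** The point holds as an unreconciled measure. Reach as tabulated is a registration count without a denominator. It combines volume with completeness of registration and does not move with consent refusal or with use of the BL/Rb modules. On the article's figures it would be about 150 whether the share of eligible children managed by protocol were 20% or 100%.

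This rests on the plan to register every patient and on the approximate 150 and 50; the numerators are illustrative. Reach is neither the primary outcome nor the named secondary one, it enters no planned test, and the comparison with historical compliance is untouched. It is a minor correction that affects how the implementation results can be read.

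**What to change.** Change the Table 4 Reach row to a proportion.

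- **Numerator:** eligible prospective patients (suspected or known BL or Rb, under 18, July 2019 to July 2020) managed with the BL or Rb protocol module. The row should state what record counts as managed with the module, since the article does not fix this.
- **Denominator:** all such eligible patients registered in mNavigator. Because eligibility includes suspected disease, it should rest on the working diagnosis or cohort assignment and not only on a confirmed diagnosis.
- **Exclusion:** the abstracted 2015–2019 records.
- **Decliners:** include them only as an aggregate count, and only once this is reconciled with the Phase 2 consent statement that research data come from consenting patients. The choice matters. If, as an assumption, 40 of 50 consent and all 40 are managed by protocol, the result is 40/50 = 80% with decliners and 40/40 = 100% without. If they must be left out, label the figure as reach among consenting patients.
- **Outside check:** compare the denominator with a source outside mNavigator if one exists. The article does not describe one. Without it, children who were never registered stay invisible, and the row should say so.

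Keep the number registered as a descriptive line labelled registrations.

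The core proportion uses data that mNavigator already collects. The cost is one reworded row, slightly more tabulation, and possibly a less favourable figure. The decliner count and the outside check are the only parts that may need further agreement or effort.

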### Statistical analysis

#### Quantitative analysis plan

Descriptive statistical measures (e.g., frequencies, means, proportions, etc.) will be generated using STATA (v15 or higher) to describe basic socio-demographic and clinical profiles of study participants. A compliance score will be generated based on the proportion of protocol steps completed. Difference-in-difference (DID) estimation will be used to track longitudinal differences in compliance from baseline to end line at BMC. For secondary outcomes, logistic regression will be used to assess provider characteristics associated with protocol compliance and completion of critical steps in the checklist. Patient characteristics at BMC will be compared using χ2 tests (binary variable) and t-tests (continuous variables).

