Finally, it mitigates concerns related to scalability of mHealth interventions by: adapting a validated, open-source mobile platform to reduce risks in the system development lifecycle and improve generalizability; using a theory-driven implementation science approach to improve contextual relevance and acceptability; and, building clinical, research, and digital health capacity at Tanzanian cancer centers, so that this and future digital interventions can be supported locally. BMC would serve as a pilot site with potential for expansion and multisite clinical research infrastructure development across Tanzania. In doing so, this study addresses criticisms of digital health systems related to poor contextual relevance, custom closed-source systems that lack inter-operability, and failure to develop appropriate local human resource capacity needed for system longevity.

Study limitations include the small sample size of mNavigator users as well as the prospective and historical patients proposed to be included in the evaluation. Since study implementation is limited to one site (BMC) based on budget and other resources available, the study sample size is limited by the availability of individuals who can participate in the study. The decision to use historical, instead of contemporary controls is also motivated by the same constraints.

Results from the evaluation of mNavigator will inform implementation and evaluation of the system in other tertiary pediatric cancer facilities in Tanzania, with the goal to facilitate protocol-driven treatment. Study findings will inform core components and elements of mNavigator, which can be adapted for use in different settings.

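### The cohort comparison takes no account of the Burkitt lymphoma to retinoblastoma mix, and the planned baseline tests cannot make up for that

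*Protocol article*

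**What the plan says.** Table 3 (Outcome measures) defines the primary effect as "Percent difference in protocol compliance with mNavigator and historical compliance". The score behind it is described thus: "Protocol compliance is calculated as proportion of protocol steps completed, based on a compliance checklist". Abandonment is "Calculated as the difference in proportion of patients registered in mNavigator who abandoned treatment compared to historical controls who abandoned treatment". Completion and time to diagnosis are likewise set directly against historical controls. No outcome in the table is split by diagnosis.

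The Quantitative analysis plan gives three further elements:
- for compliance, "Difference-in-difference (DID) estimation will be used to track longitudinal differences in compliance from baseline to end line at BMC";
- as the only regression, placed among the secondary analyses and directed at providers, "logistic regression will be used to assess provider characteristics associated with protocol compliance and completion of critical steps in the checklist";
- for the patients themselves, this sentence and nothing more: "Patient characteristics at BMC will be compared using χ2 tests (binary variable) and t-tests (continuous variables".

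The article names no covariate, stratification, matching or weighting by patient factors for the cohort effect. The Discussion says of the design that "The decision to use historical, instead of contemporary controls is also motivated by the same constraints"; it does not discuss confounding.

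**The concern.** The two cohorts are separated in time (2015 to June 2019 against July 2019 to July 2020) and are formed differently. Under Informed consent (Phase 2), prospective data are used only with consent, while historical records are exempt. Nothing in the design holds the BL:Rb mix constant across the two.

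That mix can matter. Intervention components describes separate modules with disease-specific guidelines, and the Informed consent section gives a "typical treatment duration of 3 months for patient with BL and 4 months for patient with Rb". The compliance score therefore averages over two different sets of steps. Abandonment is defined by a gap of at least four weeks while on therapy, and a longer course leaves more time for such a gap. If the mix changes between periods, the crude differences can change even if mNavigator does nothing.

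Testing baseline characteristics does not address this. A non-significant result at these sample sizes is weak evidence of balance, and the article states no consequence for a significant one.

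**Working it through.** **Inputs from the article.** About 50 prospective and 200 historical BL/Rb patients (Sample size and recruitment). No alpha, power, effect size, case mix or compliance by diagnosis is given. A two-sided 0.05 level, a BL share near 50% and the BL-Rb gap are assumptions below.

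**The article's own counts.** 150 × 0.35 = 52.5, stated as about 50. 50 per year × 4 years = 200, as stated; the Table 3 window to June 2019 is 4.5 years and would give 225. The stated 50 and 200 are used.

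**Does difference-in-difference control the mix?** The method subtracts the change in a comparison group from the change in the intervention group. Here there is one site, and the only comparator is the earlier period. With no second change to subtract, what remains is after minus before, which carries any change in case mix with it.

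**Power of the chi-square test.** Let Δ be the shift, p̄ the pooled share, p₁ the prospective share and p₀ the historical share:
- SE₀ = √[p̄(1−p̄)(1/50 + 1/200)]
- SE₁ = √[p₁(1−p₁)/50 + p₀(1−p₀)/200]
- power = Φ[(Δ − 1.96·SE₀)/SE₁]

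*BL share 50% historically, 60% prospectively.* p̄ = (30 + 100)/250 = 0.52; SE₀ = 0.0790; SE₁ = 0.0778; power = Φ[(0.10 − 0.1548)/0.0778] = Φ(−0.70) = 0.24.

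*50% historically, 65% prospectively.* p̄ = (32.5 + 100)/250 = 0.53; SE₀ = 0.0789; SE₁ = 0.0762; power = Φ[(0.15 − 0.1547)/0.0762] = Φ(−0.06) = 0.48.

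With the shares exchanged between cohorts (50% prospectively; 60% or 65% historically) the figures are 25% and 50%. Power of 80% needs a shift of about 22 points (50% to 72%). If only 40 patients consent (assumed), the 24% and 48% fall to 21% and 41%. A t-test at 50 against 200 has 24% power at a standardised difference of 0.2 and 48% at 0.3; it needs about 0.44 for 80%.

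**Effect of a mix shift with no mNavigator effect.** Pooled compliance in a cohort with BL share p is p·c_BL + (1−p)·c_Rb. If c_BL and c_Rb are the same in both periods, the crude difference equals (p₁ − p₀)(c_BL − c_Rb).

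| Shift in BL share (assumed) | BL-Rb gap (assumed) | Spurious difference |
|---|---|---|
| 10 points | 10 points | 1.0 point |
| 15 points | 20 points | 3.0 points |
| 15 points | 30 points | 4.5 points |
| 25 points | 40 points | 10.0 points |

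The direction depends on which disease has the higher score and which way the mix moves; the article informs neither.

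**The case against.** The strongest reply is that an article condenses its protocol. Table 3 defines outcomes rather than a model, and covariates may be set out in an analysis plan that is not shown. A reader might infer from the article that adjustment has been ruled out. It has not: nothing forbids it, and the plain descriptive summaries would also show imbalance. What remains is that the article states plain differences, names a set of methods, assigns its one regression to provider characteristics and gives patient characteristics only significance tests. Followed as written, that leaves the mix uncontrolled.

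A second reply is that the score is a proportion, so it is already scaled to each patient's own protocol. That removes the effect of the number of steps, but not of how hard the steps are to complete. Different steps and durations make unequal compliance possible; they do not prove it.

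A third is that the bias figures rest on assumptions, which is correct. Study setting puts existing compliance below 20%. If that is on the same scale as the score (the article does not say), then at 20% overall and a 50:50 mix a 30-point gap means 5% against 35%, and a 40-point gap means 0% against 40%. The upper rows of the table are then hard to reach.

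A reader might also infer that compliance depends on stage and that stage should be a main covariate. The article says only that staging is recorded with planned treatment. Under Quantitative data collection, historical abstraction is limited to what the paper records hold, so stage may be missing. Under Intervention delivery, completing the staging checklist is itself something mNavigator promotes. Requiring recorded stage could drop the least compliant historical patients or condition on something the intervention changes.

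Finally, this is an early-stage study and the Discussion acknowledges small samples and historical controls. That limits how much weight the point carries; but Aim 2 is to evaluate effectiveness, and the results are meant to inform other centres.

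**Conclusion.** The point holds for diagnosis. As stated, the effect measures are plain prospective-versus-historical differences over BL and Rb together, the single-site difference-in-difference does not control case mix, and the baseline tests would miss a 10-point mix shift about three times in four and a 15-point shift about half the time (two-sided 0.05, 50 against 200, BL share near 50%).

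The resulting bias cannot be sized from the article. The 3.0 to 4.5 points illustrate one set of assumptions and do not estimate what will happen. The article does not show that the mix will shift, that compliance differs between BL and Rb, or that stage drives the outcome. Against a large true effect the distortion could be minor. The change is worth making because it is cheap and removes an avoidable ambiguity.

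**What to change.** - Prespecify diagnosis (BL or Rb), age and sex as covariates in the cohort comparisons of compliance, abandonment and completion, whatever the baseline tests show.
- Report the effect within BL and within Rb alongside the adjusted overall estimate.
- Describe the compliance analysis as an adjusted before-after comparison, unless a concurrent comparison series is available.
- Use stage only in a sensitivity analysis among patients with it recorded, and report how many in each cohort lack it.

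**Cost.** Analysis wording only: diagnosis defines the patients abstracted, and age and sex are basic record items, though their completeness in the paper charts should be confirmed. The model spends a few degrees of freedom with about 50 prospective patients, and the effects within each disease will be imprecise. Adjustment does not remove secular trends between the periods, so that limitation should still be stated.
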